## Abstract

**Introduction:**

The Global Health Sector Strategy on sexually transmitted infections (STIs), endorsed by the World Health Assembly in 2016 aims to end STIs as public health threat by 2030. WHO conducts global estimates of prevalence to monitor progress towards achieving the same. However, limited laboratory confirmed data exist of STIs and reproductive tract infections (RTIs) apart from few prevalence surveys among key populations and clinic-based reports, including in India. Syndromic approach is the cornerstone of RTI/STI management and to maximise the diagnostic accuracy, there is a need to determine the main aetiologies of vaginal discharge. This study aims to estimate the prevalence of common STIs and RTIs and their aetiological organisms in symptomatic and asymptomatic women living in the urban and peri-urban, mid to low socioeconomic neighbourhoods of Delhi, North India.

**Methods and analysis:**

A cross-sectional study will be conducted among 440 married women who participated in the ‘Women and Infants Integrated Interventions for Growth Study (WINGS)’. Information on sociodemographic profile, sexual and reproductive health will be collected, followed by examination and collection of vaginal swabs for nucleic acid amplification tests to diagnose *Neisseria gonorrhoeae*, *Chlamydia trachomatis* and *Trichomonas vaginalis* and microscopy to identify bacterial vaginosis and *Candida albicans*. Treatment will be as per the syndromic approach recommendations in the Indian National Guidelines. Data will be analysed to estimate prevalence, presence of symptoms and signs associated with laboratory confirmed RTIs/STIs using STATA V.16.0 (StataCorp).

**Ethics and dissemination:**

This study protocol has been approved by the ethics review committees of the WHO and Society for Applied Studies (SAS/ERC/RHR-RTI/STI/2020). Approval has been obtained by the WINGS investigators from SAS ethics research committee to share the contact details of the participants with the investigators. The findings will be published in peer-reviewed journals and disseminated through scientific conferences.

**Trial registration number:**

CTRI/2020/03/023954.

Strengths and limitations of this studyRecent data on the prevalence of reproductive tract infection (RTI)/sexually transmitted infection (STI) and aetiologies of symptomatic RTI/STI in India are limited; this study responds to this research gap.It will provide crucial information on prevalence of laboratory confirmed *Neisseria gonorrhoeae*, *Chlamydia trachomatis* and *Trichomonas vaginalis* among asymptomatic woman, in addition to those with symptoms.This study addresses the WHO’s recommendation to periodically ascertain the aetiology of vaginal discharge syndrome every 2–3 years in order to update or modify the national guideline.This is not a community-based prevalence survey, which would require randomised sampling and would be costly.Participants in this study are limited to a prespecified cohort of women hence, generalisability of the findings and conclusions will need to be interpreted with care.

## Introduction

Sexually transmitted infections (STIs) and reproductive tract infections (RTIs) are a significant cause of global burden of disease.^1^ Of the eight pathogens of highest public health importance, four are curable, *Treponema pallidum*, *Neisseria gonorrhoeae* (NG), *Chlamydia trachomatis* (CT) and *Trichomonas vaginalis* (TV) while the other four of viral aetiology are not, hepatitis B, herpes simplex virus, HIV and human papillomavirus.^2 3^ Globally, 374 million new infections of the four curable STIs occur annually.^2 3^ These infections have significant public health consequences including infertility,^4 5^ ectopic pregnancies,^6 7^ prematurity and neonatal deaths,^8^ as well as increased risk of HIV acquisition.^9 10^ Among RTIs, bacterial vaginosis (BV) is of emerging importance as it reflects the dysbiotic state of the vaginal microbiome and increases susceptibility to other STIs.^3 4^ Candidial genital infection is the leading cause of fungal vulvo-vaginitis and asymptomatic microorganism colonisation can occur in up to 60% of the cases.^8^

Given the importance of STIs and RTIs, strengthening epidemiological data to inform management and control is imperative. In its global health strategy for the control of STIs and tool for strengthening surveillance of STIs, the WHO emphasises on four key elements, including case reporting, prevalence assessment, aetiologies and monitoring of antimicrobial resistance.^11^ Global control and prevention of STIs will contribute to progress towards achievement of the sustainable development goals to ensure universal access to sexual and reproductive healthcare services.^2^

To address the limited national data, WHO developed the STI spectrum model to assist countries to estimate the prevalence. Recent estimates suggest that incidence of STIs has plateaued at 1 million cases annually^9^; however, significant regional heterogeneity regarding the burden and availability of data exists especially in Asia and Oceania.^9^ In India, there are no recent data to determine the magnitude of STIs. Few prevalence surveys among key populations and pregnant women exist to inform national STI estimates. Regular case reporting of infections such as gonorrhoea is available, but are under-reported, thus the generation of more accurate prevalence data among the general population is needed. Apart from regular case reporting, WHO recommends studies to determine local aetiologies of STIs every 2–3 years to improve management.^10^

In India, it is estimated that 6% of the adult population is infected with one or more STIs at any one time. Due to limited access and affordability of STI laboratory diagnosis at the primary level of care where majority of STI cases seek care, syndromic case management remains the cornerstone of STI control.^12^ This, as is the case in many low-income and middle-income countries is partly due to its lower infrastructural/equipment investments and limited availability of expertise. Syndromic approach is based on presence of signs and symptoms reported, and provides immediate treatment for the most common organisms causing the identified syndrome through the use of pre-packaged colour coded drug kits. It is also recommended for the pregnant women.

Based on new evidence, WHO recommends quality-assured molecular assays for treatment of people with symptoms of NG, CT and TV. If quality-assured molecular assays are not available, treatment-based syndromic approach is recommended.^13^ However, syndromic approach has certain limitations. It results in over treatment or missed diagnosis of cervical infections (NG and/or CT) compared with aetiological approach using molecular assay.^14 15^ While aetiological determination of STI is more accurate, it is often not feasible in most health facilities. Aetiological data among symptomatic and asymptomatic women are inadequate across India.^14^ Of the few studies that have explored aetiologies of vaginal discharge, the focus has been among sex workers in 2003 and 2011,^14 15^ and these studies found high rates of STIs, especially NG and CT. In 2009, a comparative study of syndromic and aetiologic diagnosis of STIs was conducted among general population in Delhi^16^ that included symptomatic and asymptomatic pregnant and non-pregnant women. It revealed a high proportion of women complaining of vaginal discharge, self-reporting of morbidity (65%) and presence of sexually transmitted disease-related syndrome (71.4%). The aetiological microorganism was established in 32.2% of the cases. Our study intends to build on these findings to generate more detailed quality-assured data related to aetiologies of RTI/STIs among symptomatic and asymptomatic women.

## Methods

### Aims and objectives

The overall aim of the study is to generate information and data related to RTI/STIs among women in India. More specifically, there are three objectives. First, to determine the prevalence of NG, CT, TV, BV and *Candida albicans* (CA) among women residing in the peri-urban and urban mid to low socioeconomic areas of South Delhi at least 14 days after they exit from Women and Infants Integrated Interventions for Growth Study (WINGS). Second, to assess the diagnostic validity of the current RTI/STI syndromic case management practice relative to the aetiologic diagnosis based on laboratory confirmation of NG, CT, TV, BV and CA among symptomatic and asymptomatic women. Third, to identify demographic, behavioural, sexual and clinical factors associated with laboratory confirmed RTI/STI among women. Similar data on syphilis are already being collected as a part of WINGS.^17^

### Study design and participants

This is a cross-sectional independent study enrolling women at least 14 days after their exit from WINGS. WINGS was an individually randomised factorial trial to assess impact of a package of community level health, nutrition, WASH and psychosocial care interventions delivered in preconception, during pregnancy and in the first 2 years after birth, on birth outcomes and infant growth. Thirteen thousand and five hundred married women aged 18–30 years, living with their husband with no or one child, and wanting more children, were enrolled and randomised to receive a pre-conception intervention package or routine care, until pregnant or 18 months post-enrolment. At pregnancy confirmation, second randomisation was done to receive pregnancy and early childhood interventions or routine care. This resulted in four groups of women that received (1) preconception, pregnancy and early childhood interventions, (2) only pre-conception interventions, (3) only pregnancy and early childhood intervention and (4) no interventions.

Women will be exiting WINGS at two time points: at 18 months since enrolment for women who do not get pregnant, or at 24 months postdelivery for women who get pregnant. A more detailed protocol for WINGS was published elsewhere.^17^

### Sample size

Overall, 6% of adults in India are estimated to have STIs.^14^ Existing studies suggest that 32% of cases have laboratory confirmed STI.^16^ Therefore, a sample size of 440 women will be adequate to ascertain the prevalence of aetiological diagnosis of STI in symptomatic and asymptomatic women with 95% confidence, 15% relative precision and 20% non-response rate allowance.

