### Statistical analysis and outcome measures

Descriptive and inferential statistical analysis will be performed. Simple proportions and 95% confidence bounds will be calculated to determine prevalence for overall laboratory confirmed RTI/STI and individual microorganism by binomial exact method. We will use a method of purposeful selection of covariates to identify variables for the multivariable models.^23 24^ In the multivariable models, we will include the variables that will change the OR of the outcome variables by 20% from the univariable models. We will present the adjusted models, including variables that will be identified in the procedure. We will assess whether any of the demographic, behavioural, sexual and clinical risk factors are modifying the association between laboratory conformed RTI/STI and any of the abovementioned variables on a multiplicative scale. Computation of sensitivity, specificity, predictive values and likelihood ratios will be derived in diagnosing vaginal infection (TV, BV) and cervical infection (NG, CT) using NAAT as the gold standard of diagnosis compared with syndromic approach which is informed by the presence of symptoms and signs. Analysis will be done using STATA V.16.0 (StataCorp).

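### The 15% relative precision claimed for 440 women holds only for one pooled proportion near 32%; at the 6% STI figure in the same paragraph it is about 37% to 41%

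*Protocol article*

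**What the plan says.** The Sample size section gives two background proportions. The first is "Overall, 6% of adults in India are estimated to have STIs". The second, taken from the 2009 Delhi study, is "32% of cases have laboratory confirmed STI". It then concludes that "a sample size of 440 women will be adequate to ascertain the prevalence of aetiological diagnosis of STI in symptomatic and asymptomatic women". The criteria attached to this conclusion are given as "95% confidence, 15% relative precision and 20% non-response rate allowance". The section does not say which proportion produced 440.

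The Introduction reports the second figure differently: "The aetiological microorganism was established in 32.2% of the cases". It also explains that the 6% refers to adults carrying at least one STI at a given time.

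The first objective (Aims and objectives) is "to determine the prevalence of NG, CT, TV, BV and" *Candida albicans*. The Statistical analysis section plans exact 95% bounds "to determine prevalence for overall laboratory confirmed RTI/STI and individual microorganism by binomial exact method". The Abstract states the aim as to "estimate the prevalence of common STIs and RTIs and their aetiological organisms in symptomatic and asymptomatic women".

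**The concern.** Relative precision depends strongly on the prevalence assumed. A sample that gives 15% relative precision at 32% gives much less at 6%. The adequacy statement is attached to STI, and the only STI prevalence the paragraph gives for a general population is 6%. The 32% is a share of cases, and the Introduction does not describe it as an STI prevalence in all women.

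The study is meant to inform national STI case management. A reader who takes the sentence at face value would expect estimates for STI, and for NG, CT and TV separately, to be accurate to within 15% of their value. At the document's own STI figure they would not be.

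**Working it through.** **Inputs.** From the Sample size section: proportions 32% and 6%, relative half-width r = 0.15, 95% confidence (z = 1.96), 20% non-response, N = 440. If 20% of 440 are lost, 440 × 0.8 = 352 women are evaluable. If 440 is read as the number examined, 440 are evaluable. Both are shown.

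**Step 1: reproduce 440.** For one proportion, n = z²(1 − p) / (p r²).

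- p = 0.32: n = 1.96² × 0.68 / (0.32 × 0.0225) = 362.8, so 363. Then 363 × 1.2 = 436, which rounds to 440; 363 / 0.8 = 454.
- p = 0.322: n = 360; × 1.2 = 432; / 0.8 = 450.
- p = 0.06: n = 1.96² × 0.94 / (0.06 × 0.0225) ≈ 2,675; × 1.2 = 3,210; / 0.8 = 3,344.

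So 440 comes from one pooled proportion of about 32%. The 6% cannot produce it.

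**Step 2: precision that 440 women give.** Relative half-width = z √[(1 − p) / (pN)]; the absolute half-width is this times p.

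| Prevalence | 352 evaluable | 440 evaluable |
|---|---|---|
| 32% | 15.2% relative (4.9 points) | 13.6% relative (4.4 points) |
| 6% | 41.3% relative (2.5 points) | 37.0% relative (2.2 points) |

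At 6%, 352 women yield about 21 cases (0.06 × 352 = 21.1). The exact interval for 21/352, the method the plan specifies, is 3.7% to 9.0%.

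**Step 3: where 15% is met.** Solving the formula for p gives p = z² / (z² + N r²).

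- N = 352: 3.84 / (3.84 + 7.92) = 32.7%.
- N = 440: 3.84 / (3.84 + 9.90) = 28.0%.

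Any organism with a prevalence below these values is estimated less precisely than 15%. The 6% covers one or more STIs, so at that level no single STI can exceed 6%.

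**Step 4: symptom groups, only if such estimates are intended.** The shares are assumptions; the protocol plans no split. At an assumed 32% in both groups with 352 evaluable women:

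- 50/50 split (176 each): 21.5% relative in each group.
- 65/35 split (229 and 123; 65% is the self-reported morbidity in the 2009 Delhi study): 18.9% and 25.7%.

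Reaching 15% in two equal groups would take 2 × 363 = 726 evaluable women.

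**The case against.** Several points on the other side have force.

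- **The number is not miscalculated.** A reader might infer an arithmetic error in 440. There is none: it follows from 32% with a factor of 1.2, and 32.2% divided by 0.8 gives 450, which is close. The choice of non-response formula only moves the pooled precision from 15.0% (363 evaluable) to 15.2% (352). The Abstract can also be read as 440 women actually studied, and then the pooled precision at 32% is 13.6%, better than claimed.
- **The symptom groups may be pooled.** A reader might infer that 15% is promised separately for symptomatic and asymptomatic women. The phrase can simply name the enrolled population, and the Statistical analysis section plans no prevalence by symptom status. Only a bullet under Strengths and limitations points to separate information on asymptomatic women, and it states no precision.
- **What the 32% counts is not fully known.** A reader might infer that it is an any-organism composite that includes BV and *Candida*. The Introduction does not list the organisms counted or define the cases, so this remains an inference. What the text does show is that the figure is a share of cases.
- **The 6% is a national background figure.** It is not specific to NG, CT and TV in married women, and the plan does not expressly attach the 15% to it.
- **Absolute precision is better at low prevalence.** It is ±2.5 points at 6% against ±4.9 points at 32%, and the planned exact bounds will show the actual uncertainty.

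These points narrow the concern but do not remove it. The paragraph chose relative precision as its criterion, applied it to STI, and cited 6% as the STI prevalence. On that criterion the claim fails at that figure under either reading of 440.

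**Conclusion.** The adequacy statement is wrong as written because it reaches further than its calculation. The calculation supports 15% relative precision for one pooled proportion of about 32%. It does not support it for STI at 6%, where the relative half-width is 37% to 41%, or for any organism whose prevalence is below about 28% (440 evaluable) to 33% (352 evaluable). The conclusion rests on the document's own 32%, 6%, 15% and 20%, and on the normal approximation; the exact interval at 6% agrees with it. BV or *Candida* could meet the target if common enough; the document gives no expected prevalence for them.

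This is a misstated design property in one paragraph. It does not bias the prevalence estimates or invalidate the planned analysis. The symptom-group figures apply only if such estimates are intended, and the non-response formula is a minor point.

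**What to change.** Keep enrolment at 440 and reword the Sample size paragraph so that it:

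1. Names 32% as the assumption behind 440, describes it as the Introduction does (share of cases with an organism established), and acknowledges that applying it to all enrolled women is an assumption.
2. Limits the 15% claim to the pooled estimate of any laboratory-confirmed RTI/STI, if that is 32%: 15.2% relative with 352 evaluable women, 13.6% with 440.
3. States the expected precision for STI at 6%: ±2.2 to 2.5 points, or 37% to 41% relative.
4. Says that estimates for single organisms at lower prevalence will be less precise than 15%.
5. If estimates by symptom status are intended, says that 15% does not hold within groups. At an assumed 32% with 352 evaluable women it is about 21.5% in each for a 50/50 split, or 19% and 26% for an assumed 65/35 split.
6. States whether 440 is the number approached or the number evaluable.

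The cost is one reworded paragraph and a less favourable stated precision. No additional women and no change to the analysis are needed.

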### Study procedures

Study preparatory activity started in January 2021 and is expected to be completed in December 2022.

### Recruitment

Study participants who exit from WINGS will be contacted after at least 14 days to ascertain their willingness to participate and those who agree will be offered to take part in the study.

### Informed consent

Written individual informed consent will be obtained from all study participants at enrolment for quantitative data collection, collection of endocervical swabs and for interviews by research assistants at the study clinic. For those who are unable to read, the consent form will be read out by the worker. Those participants who are unable to sign, a thumb imprint will be taken and witnessed (counter signed) by an impartial literate witness. The informed consent form will be translated into simple Hindi language that can be easily read and understood.

### Inclusion criteria

Women who exit WINGS study, give consent and are eligible for sampling. Eligibility is ascertained through screening. Women are screened out and visit rescheduled if they are menstruating at the time of screening, have history of vaginal douching, usage of any vaginal tablets or cream and had sexual intercourse in the last 48 hours. Blood, semen or medication can potentially interfere with test results.

### Exclusion criteria

Women who exit WING study but decline to consent.

### Data collection

Using a structured questionnaire, the research assistants will conduct face-to-face interviews to collect information on sociodemographic, economic and sexual behaviour. The sociodemographic and economic questionnaire includes information on educational status, occupation, family size and structure, annual income, number of family members, religion, household assets, health insurance cover and WASH practices. Questionnaire on sexual behaviour includes information on age of first intercourse, number of partners, use of barrier methods, symptoms of RTI/STI in previous 1 week, history of RTI/STIs and treatment received during last 3 months, among other data.

### Gynaecological examination

A thorough history and genital and pelvic examination including abdominal palpation will be done by the study gynaecologist with aseptic precautions in complete privacy, for all participants irrespective of the symptoms. With the participant in the dorsal lithotomy position, a visual inspection of the external genitalia, followed by a per speculum and bimanual examination will be done.

Signs of RTI/STI and other observations will be documented in an electronic tracker. These will include nature of vaginal discharge (ie, colour, odour, consistency, amount), presence and type of cervical discharge, condition of cervix, any genital ulcers, adnexal or pelvic tenderness, size of uterus, any adnexal mass or lump. High vaginal swab and endo-cervical swab will be collected as per the standard operating procedures. Women will be provided free medication according to the diagnosis, as per the National Guidelines on RTI/STI.^18^

### Sample collection, storage and transportation

Two swabs will be collected, one vaginal and other endocervical, by the study gynaecologist. The vaginal walls and cervix will be visualised using self-retaining sterile Cusco’s speculum. Vaginal swab specimen will be collected from the posterior fornix and the lateral walls of the vagina for detection of BV and CA and kept in a pre-labelled dry collection tube. Following this, the endocervical swab from the test kit will be inserted gently into the endocervical canal, rotated and withdrawn and kept in the pre-labelled transport reagent container for nucleic acid amplification test (NAAT) for CT, NG and TV.

All samples will be stored at 2°C–8°C in the laboratory and transportation to the testing laboratory will be done daily, in cool boxes maintained at 2°C–8°C.

### Laboratory procedures

NAAT, a real-time PCR having the highest specificity and sensitivity (98%–100%) among the available conventional tests, will be used to detect CT, NG and TV.^19^ We will use cartridge based (CB) NAAT Gene Xpert platform which is an automated in vitro diagnostic (IVD) test for qualitative detection and differentiation of DNA of CT, NG and TV and is performed on Cepheid GeneXpert Instrument Systems.^20^ With this we will use the GeneXpert CT/NG Cepheid IVD, and GeneXpert TV Cepheid IVD kits.^21^

The GeneXpert Instrument Systems automate and integrate DNA extraction, amplification and detection of the target sequences in simple or complex samples using reverse transcription (RT-PCR). The systems consist of an instrument connected with a computer, with preloaded software for running tests and viewing and generating results. The systems require single-use disposable cartridges that hold the PCR reagents and host the PCR process.

Reagents for the detection of a Sample Processing Control (SPC), a Sample Adequacy Control (SAC) and a Probe Check Control (PCC) are also included in the cartridge. The SPC is present to control for adequate processing of the target bacteria and to monitor the presence of inhibitors in the PCR.

The SAC reagents detect the presence of a single copy human gene and monitor whether the sample contains human DNA. The PCC verifies reagent rehydration, PCR tube filling in the cartridge probe integrity and dye stability. The primers and probes in the Xpert CT/NG test detect chromosomal sequences in the bacteria. One target is detected for CT (CT1) and two different targets are detected for NG (NG2 and NG4). Both NG targets need to be positive for the Xpert CT/NG test to return a positive NG result. Prepared sample is transferred to the sample chamber of the Gene expert cartridge and loaded on the GeneXpert machine and the test is performed.

Summary and detailed test results are generated by the software in approximately 90 min and are displayed in tabular and graphic formats. Nugent’s scoring criteria using a gram-stained slide is the current gold standard with ~77% specificity and 90% sensitivity will be used to diagnose BV.^22^

A smear will be prepared, and gram staining done. Microscopic examination will be done to detect clue cells and semi-quantitative evaluation for gram-positive, gram-negative or gram-variable bacterial morphotypes quantified. Women will be categorised as non-BV (Nugent Score 0–3), intermediate (Nugent Score 4–6) or BV (Nugent Score ≥ 7) (table 1).

**Table 1 T1:** Nugent score

Organism morphotype	Number/oil immersion field	Score
Lactobacillus-like (parallel sided, gram-positive rods)	>30	0
	5–30	1
	1–4	2
	<1	3
	0	4
Mobiluncus-like (curved, gram-negative rods)	>5	2
	<1.4	1
	0	0
Gardnerella/bacteroides-like (tiny, gram variable coccobacilli and pleomorphic rods with vacuoles	>30	4
	5–30	3
	1–4	2
	<1	1
	0	0

Total score: 0–3=normal; 4–6=intermediate, repeat test later; 7–10=bacterial vaginosis.

Microscopical examination of the vaginal smear will be done for yeast cells with pseudo hyphae to detect CA.

Complete reports will be generated and sent after 48 hours.

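### The plan names *Candida albicans* prevalence as an outcome, but its only test, smear microscopy for yeast with pseudohyphae, does not identify species

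*Protocol article*

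**What the plan says.** Aims and objectives in the protocol article sets as the first objective "to determine the prevalence of NG, CT, TV, BV and *Candida albicans* (CA) among women". *C. albicans* is thus a target at species level, alongside four other infections. Statistical analysis and outcome measures then plans a simple proportion with exact binomial 95% limits for each microorganism and for any laboratory-confirmed infection.

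The test is described in three places, and they agree:

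- The Methods and analysis paragraph of the abstract assigns bacterial vaginosis and *C. albicans* to microscopy.
- Sample collection, storage and transportation takes one vaginal swab "for detection of BV and CA and kept in a pre-labelled dry collection tube".
- Laboratory procedures gives the criterion: "Microscopical examination of the vaginal smear will be done for yeast cells with pseudo hyphae to detect CA".

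The nucleic acid test "will be used to detect CT, NG and TV" and has no Candida target. The article describes no culture or other species-identifying step. It gives accuracy figures for the nucleic acid test (98%–100%) and for Nugent scoring (about 77% specificity, 90% sensitivity), but none for yeast microscopy.

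**The concern.** The outcome carries the name of a species, while the measurement records a shape seen under the microscope. That yeast morphology on a stained smear does not establish species is general laboratory knowledge and needs no outside figure.

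Against the named target there are two possible errors:

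- A yeast of another species that forms pseudohyphae is counted as *C. albicans* (false positive).
- *C. albicans* present only as yeast or budding cells does not meet the stated criterion and would apparently be counted negative (false negative).

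The article presents the study as a source of laboratory-confirmed aetiology for national guidance. Followed as written, it would publish a species-specific prevalence that the test cannot support. The exact binomial interval would describe sampling error around a different quantity.

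**Working it through.** **1. Target against test.** Every stated target was set beside its stated test.

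| Target | Test described | Does the test identify the named target? |
|---|---|---|
| NG, CT, TV | Nucleic acid amplification | Yes, organism-specific |
| Bacterial vaginosis | Nugent score on Gram stain | Yes, the target is a condition defined by the score |
| *C. albicans* | Yeast cells with pseudohyphae on smear | No, morphology only |

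Only the last row pairs a species name with a test that does not identify species.

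**2. Possible smear results, judged against *C. albicans*.**

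| In the sample | Smear | Counted as | Correct for *C. albicans*? |
|---|---|---|---|
| *C. albicans* with pseudohyphae | positive | CA | yes |
| *C. albicans*, yeast form only | no pseudohyphae | apparently not CA | no, missed |
| Other species with pseudohyphae | positive | CA | no, mislabelled |
| Other species, yeast form only | no pseudohyphae | apparently not CA | yes |

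The errors in rows 2 and 3 pull the estimate in opposite directions. The word *apparently* is needed because the article says what the microscopist looks for, but not how yeast without pseudohyphae is scored.

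**3. The plan's own sample size, for scale.** Inputs from Sample size: p = 0.32, 95% confidence (z = 1.96), 15% relative precision, so d = 0.15 × 0.32 = 0.048, and a 20% allowance.

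n = z²p(1 − p)/d² = 1.96² × 0.32 × 0.68 / 0.048² = 362.8, rounded up to 363. Then 363 × 1.20 = 436, close to the stated 440. The figure is reproduced approximately, and the present point does not depend on it. The value 363 is used below only for a sampling half-width.

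**4. Illustration under assumed accuracy.** The documents give no sensitivity (Se) or specificity (Sp) of the smear for *C. albicans*. The assumed ranges are Se 40–80% and Sp 95–100%. With true prevalence π:

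observed = π·Se + (1 − π)(1 − Sp), so π = (observed + Sp − 1)/(Se + Sp − 1).

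- Observed 10%: lowest π = (0.10 + 0.95 − 1)/(0.80 + 0.95 − 1) = 0.05/0.75 = 6.7%; highest π = 0.10/0.40 = 25%. Sampling half-width: 1.96 × √(0.10 × 0.90/363) = 3.1 points.
- Observed 5%: lowest π = 0; highest π = 0.05/0.40 = 12.5%. Sampling half-width: 2.2 points.
- In the other direction, true π = 10%: observed runs from 0.10 × 0.40 = 4.0% (Sp 100%) to 0.10 × 0.80 + 0.90 × 0.05 = 12.5% (Sp 95%).

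The last line shows that even the sign of the net error is open: within these assumptions the observed value can lie below or above the truth.

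**The case against.** **The criterion may be a deliberate case definition.** The Introduction separates Candida infection from carriage and says that "asymptomatic microorganism colonisation can occur in up to 60% of the cases". Requiring pseudohyphae could be a way to avoid counting colonised women as infected. This stands as a defence of the criterion. It does not rescue the species name: on that reading the outcome is candidiasis defined by microscopy. It also means that the Introduction's figure cannot be used as evidence of undercounting, since it can be read either way.

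**The article is a condensed document.** The full protocol may say how yeast without pseudohyphae is recorded, so the missed-case error is an inference. The mismatch of name and test does not rest on silence, however. The article states the method positively, and the abstract and the laboratory section agree. If the full protocol contains a species-identifying test, the point falls and the article should say so.

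**Stronger readings that a reader might infer, and that the documents do not support:**

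- *That no usable Candida result can be derived.* The criterion and the estimator together give a valid proportion for yeast with pseudohyphae on smear.
- *That mislabelled species corrupt the composite.* A yeast infection given the wrong species name still belongs in a composite of laboratory-confirmed infections.
- *That the accuracy results for syndromic management are affected.* The second objective does list CA, but the accuracy analysis in Statistical analysis and outcome measures names only TV, BV, NG and CT. As written, no sensitivity, specificity or predictive value is computed for CA.
- *That a count of misclassified women can be given.* Applying an assumed share of other species to all Candida carriers would count as errors the women in the last row of the second table, who are classified correctly.

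**Conclusion.** The point holds as a mismatch between the named outcome and its test, and it is wrong as written. The planned figure estimates the prevalence of yeast with pseudohyphae on a stained smear, not the prevalence of *C. albicans*.

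The net error cannot be derived from the documents. The range of about 7% to 25% for an observed 10% rests entirely on assumed accuracy. It shows only that classification error could exceed the sampling error that the planned interval reports. Confidence is high on the label and low on whether the numerical bias is material. One of the five named infections is affected.

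**What to change.** In the abstract (Methods and analysis), Aims and objectives, Laboratory procedures, and Statistical analysis and outcome measures, name the outcome *vaginal yeast with pseudohyphae (Candida morphology) on Gram-stained smear*, with no species claim. Keep that one definition in the composite of laboratory-confirmed RTI/STI.

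On the same slide, also record whether any yeast or budding cells are seen without pseudohyphae. Report that proportion as a secondary or sensitivity estimate, so that readers can see how far the result depends on the pseudohyphae criterion.

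The cost is the loss of the species-level claim, a change of wording and one extra recorded field on a slide that is already being read. No new swab or assay is needed. If slides have already been read without the extra field, the renaming can still be made alone.
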